### Design

The study will use a three group, randomized, open-label controlled clinical trial study design.

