### Trial procedures

All participants will be asked to attend up to five study visits and to monitor their smoking using a modified smart-phone for a total of four weeks. Primary data collection will take place via the customized smart-phone (described below), with additional information obtained via questionnaires at study visits. All measures have been used and validated in the context of previous smoking studies.

At the beginning of the enrollment visit (Visit 1) eligible and interested smokers will be given a detailed overview of the study requirements and asked to provide written informed consent. Participants will then be randomized to their treatment group and assigned a quit date that will fall 17 days after initial enrolment. Participants will be instructed to quit smoking completely on their assigned quit day. During the initial visit participants will also provide two expired air carbon monoxide (CO) samples (see below), and a urine sample.

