During the pre-quit monitoring phase (i.e., Visit 1–3), the phone will be used to administer three types of assessments. Firstly, following 4–5 randomly selected cigarette reports per day, participants will be asked to complete an assessment of their current state (mood, withdrawal severity, craving etc.) as well as contextual and situational details (where the participants is, who they are with, what they are doing etc.). In addition to these “smoking assessments” the device is programmed to “beep” participants at a rate of approximately 4–5 times per day for randomly-selected non-smoking assessments (“random assessments”). During these assessments, participants will complete a series of items that parallels those administered during smoking assessments. Finally, participants will also complete end-of-day assessments to gather global reports on daily mood, craving and quitting self-efficacy. The two weeks of post-quit EMA monitoring will closely mirror that used in baseline monitoring, however post-quit assessments will include additional items pertaining to the lapse trigger(s) and the use (if any) of coping mechanisms [21]. Items in the proposed EMA assessments have been used and validated in previous EMA studies, and are reported in detail in resulting publications [21, 34]. Participants will be trained in EMA procedures and on assessment content before field monitoring commences formally (during Visit 1). Following procedures established in previous successful EMA studies [21], the second study visit (Visit 2) will be scheduled 2–4 days after participants start EMA field monitoring, at which time their data will be downloaded and checked, and they will receive further EMA training (if necessary). At the end of EMA monitoring (Visit 4) the study phones will be retrieved and re-used with subsequent participants.

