#### Study visits 2–5

Participants will complete a further 4 study visits as part of the study. During each of these visits, CO and urine samples will be obtained for all participants, and satisfaction with smoking will be assessed using the mCEQ. During Visit 2 (14 days prior to quit day), participants in the Standard Patch group will be provided with one patch, which they will be instructed to apply on the morning of their assigned quit day. EMA data will be downloaded from all participants and checked for compliance, with extra training provided if necessary. Visit 3 will occur on a participants target quit day (17 days after enrollment). During this visit, in addition to the general tasks described above EMA data will be downloaded and checked for protocol compliance with additional training provided if necessary.

Study Visit 4 will occur 14 days after quit day and will mark the end of the EMA monitoring period and all phones will be handed back. The final study visit (Visit 5) will occur 28 days after participants target quit day. Participants who self-report 7-day point prevalent abstinence at this visit, verified by expired air CO (see below), will be provided a further six weeks of study medication. In addition to the general study visit tasks, during their final study visit participants will then complete an exit interview during which they will be asked about the study interventions and their experiences in the study. They will also be fully debriefed and offered the opportunity to ask any final questions about the study.

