### Analytic plan

The proposed sample size (*n* = 216; 72 participants per group) was determined by the requirements of the primary research questions—namely, detecting reductions in satisfaction (H1) and craving (H2) scores, and smoking rate (H3), between the Standard Patch and the two pre-quit treatment groups at the end of the pre-quit treatment period (Visit 3). In a previous study [19] we observed moderate-to-large effects of pre-quit nicotine patch treatment on self-reported satisfaction with smoking, craving, and smoking rate during the pre-quit treatment period. Using these reductions as a proxy for between-group differences (assuming that these measures will not decrease during the pre-quit period for participants in the Standard Patch group), a conservative estimate of within-subject correlation of measures (0.5), our proposed sample will afford >90 % power to detect a difference in these measures. Our proposed sample size will also afford >80 % power to detect an effect of smoking reduction during the pre-quit phase on treatment outcomes (assessed at Visit 5; H4). Based on an earlier study [19] we expect to see ~6 % dropout before Visit 3 and as such we aim to recruit and enroll 229 participants in order to achieve our evaluable sample.

Our primary research questions involve reductions in satisfaction with smoking (H1), cigarette craving (H2), and smoking rate (H3) during the pre-quit treatment phase. These questions will be tested separately for each of the pre-quit groups using data gathered from the EMA field monitoring using mixed models growth curve analyses. The effect of smoking reduction on abstinence (H4) will be assessed in two ways. Firstly, reduction during the pre-quit phase will be used in a logistic regression model to predict biochemically verified 7-day point prevalent abstinence at Visit 5 (4 week abstinence). Treatment group will be included as a covariate. This outcome analysis will be conducted as intent-to-treat, with all participants who are randomized (Visit 2) being included in the analyses. Study dropouts will be counted as treatment failures. Next, as traditional intent-to-treat point prevalent abstinence analyses can obscure important aspects of the process of quitting smoking [13, 35], we will also use the real-time EMA data to examine time to first lapse using survival analyses.

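### Randomisation is placed at Visit 1 in the procedures but at Visit 2 in the intent-to-treat definition for the H4 abstinence analysis; one visit must be stated and the set tied to it

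*Protocol article*

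**What the plan says.** Trial procedures opens its account of the enrolment visit with "At the beginning of the enrollment visit (Visit 1) eligible and interested smokers will be given a detailed overview of the study requirements". Consent follows, and then: "Participants will then be randomized to their treatment group and assigned a quit date that will fall 17 days after initial enrolment". The next sentence there still concerns the initial visit. On this account randomisation is a Visit 1 event, 17 days before quit day.

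The Analytic plan says that the logistic regression for H4 (pre-quit smoking reduction predicting verified abstinence at Visit 5, with treatment group as a covariate) will be intent-to-treat, "with all participants who are randomized (Visit 2) being included in the analyses". It adds: "Study dropouts will be counted as treatment failures".

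Visit 2 is a separate, later visit. The EMA section says "the second study visit (Visit 2) will be scheduled 2–4 days after participants start EMA field monitoring", and Study visits 2–5 says "During Visit 2 (14 days prior to quit day), participants in the Standard Patch group will be provided with one patch". The Design section makes the trial open-label: "The study will use a three group, randomized, open-label controlled clinical trial study design".

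**The concern.** Both statements are current text, and they cannot both be right about when randomisation happens. One of them sits inside the sentence that defines an analysis set, so the conflict is more than a slip in the visit schedule.

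Suppose allocation follows Trial procedures and the set is assembled from Visit 2 attenders. A participant who is randomised, leaves within a few days and never reaches Visit 2 is then neither in the denominator nor counted as a failure. That is an exclusion after randomisation in an analysis labelled intent-to-treat. Because the trial is open-label and one arm receives no medication for the two pre-quit weeks, early departure could plausibly differ by arm. The conflict also leaves open whether the 229 to be enrolled are the same people as those randomised.

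**Working it through.** **1. The two times side by side**

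| Source in the protocol article | Randomisation | Days before quit day |
|---|---|---|
| Trial procedures | Visit 1, after consent | 17 |
| Analytic plan | Visit 2 | 14 (from Study visits 2–5) |

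The gap is 17 − 14 = 3 days, which agrees with the 2 to 4 days in the EMA section. The visit calendar is coherent; only the randomisation point conflicts. Study visits 2–5 does not list randomisation among the Visit 2 tasks.

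**2. The plan's own enrolment figure**

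Inputs from the Analytic plan: 216 evaluable, about 6% dropout before Visit 3, 229 to be enrolled.

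- 216 / (1 − 0.06) = 229.8
- 216 × 1.06 = 228.96, rounded up to 229

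The stated 229 is reproduced to within one participant, so 229 and 6% can be used below.

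**3. How many could fall out of the set**

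The loss between Visits 1 and 2 is not stated. It cannot exceed the expected loss before Visit 3.

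- Lower limit: 0, leaving 229.
- Upper limit: 0.06 × 229 = 13.7, about 14, leaving about 215.
- Assuming a constant dropout rate over the 17 days: 14 × 3/17 = 2.5 across all three arms. With the gap at 2 or 4 days: 14 × 2/17 = 1.6 or 14 × 4/17 = 3.3.

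**4. What that does to a crude abstinence proportion**

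Assumptions: 229/3 ≈ 76 per arm and 30% abstinent, with every early leaver a non-abstainer. The 30% is illustrative; the Background says that about 70% of quit efforts fail even with the best current treatment. The expected number abstinent is 0.30 × 76 = 22.8.

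| Early leavers omitted from one arm | Proportion abstinent |
|---|---|
| 0 | 22.8/76 = 30.0% |
| 1 | 22.8/75 = 30.4% |
| 2 | 22.8/74 = 30.8% |
| 2.5 (all expected losses in one arm) | 22.8/73.5 = 31.0% |
| 5 | 22.8/71 = 32.1% |

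If the 2.5 are spread evenly, about 0.8 per arm, each arm moves to 22.8/75.2 = 30.3% and no difference between arms is created.

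These are crude proportions. They show the scale of the shift but are not an estimate of bias in the H4 coefficient.

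**The case against.** The strongest reply is that the operative words include everyone who is randomised, and that the bracketed visit only notes when this was thought to happen. On that reading nobody is lost. If randomisation is at Visit 2, every randomised participant is in the set. If it is at Visit 1, the bracket is simply wrong and the set is still everyone randomised. This stands in part: the exclusion is conditional, and the rule that dropouts count as failures remains in the text. It does not remove the conflict, because a programmer building the set could follow either the words or the bracket.

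The second reply is that little depends on it. The sentence governs only the H4 regression, where treatment group is a covariate, and none of the four hypotheses compares abstinence between arms. Someone who leaves before Visit 2 also has no data from the two-week treatment phase, so their smoking reduction cannot be observed however the set is defined. This stands, and it limits the severity.

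A reader might infer more than the document supports:

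- **That the plan does exclude participants who already know their arm.** No section says when participants are told their group. Disclosure at Visit 1 is an inference from the open-label design and Trial procedures.
- **That the abstinence result would be materially distorted.** This needs a large share of the pre-Visit-3 dropout to fall in about 3 of 17 days and in a single arm, which is close to a worst case.
- **That the Visit 1–2 monitoring days are a compromised untreated baseline.** The document does not designate those days as the baseline for H1–H4, and the Standard Patch group is untreated throughout the pre-quit period. Expectancy in an open-label trial also acts throughout that period, so moving allocation by about 3 days would not remove it.
- **That randomisation ought to be at Visit 2.** Randomising at enrolment is not an error in itself.

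**Conclusion.** The concern holds as an internal contradiction. Two sections put randomisation at different visits, about 3 days apart, and one of them defines the intent-to-treat set for H4. The document does not show which is right.

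Harm arises only if randomisation is at Visit 1 and the set is counted from Visit 2. In that case between 0 and about 14 of 229 randomised participants would be left out, or about 2 to 3 on the assumption of even dropout over 17 days. The effect on H4 is probably small. The intent-to-treat sentence does not govern H1–H3, and no sample-size or power figure is affected. The correction is still worth making before analysis, because the time of randomisation and the membership of the intent-to-treat set should not be open to two readings.

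**What to change.** State the one visit at which randomisation actually takes place and make Trial procedures and the Analytic plan agree. Define the intent-to-treat set for H4 as everyone randomised at that visit, with all later dropouts counted as failures, as is already planned.

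- If randomisation is at Visit 1: delete the bracketed Visit 2 from the Analytic plan, so that anyone who leaves between Visits 1 and 2 stays in the set as a failure.
- If randomisation is at Visit 2: correct the sentence in Trial procedures. People who leave before Visit 2 were then never randomised and are properly outside the set.

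The cost is one sentence. It needs no added visit, procedure or participant and no change to the design.

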## Discussion

This study is designed to test the mechanism(s) though which pre-quit treatments—specifically nicotine patches and varenicline—aid cessation. Understanding how these two pre-quit treatments influence abstinence may allow for better tailoring of these efficacious treatments. Additionally, understanding the effects of pre-quit treatment with nicotine patch and varenicline may provide targets for new pharmacotherapies.

## Ethics and research governance

The project was reviewed and approved by the Tasmanian Health and Medical Research Ethics Committee (H0013619) prior to starting the recruitment process. Written informed consent will be obtained from all participants.
